#### Subgroup analysis

Subgroup analysis will be carried out with respect to age, gender, duration of illness, and sex by adding a treatment with covariate interaction into the primary analysis model. Gender and sex will be included in separate models to evaluate independent impact.

#### Cost-effectiveness analysis

We will undertake an economic evaluation of a culturally appropriate psychosocial intervention, where the target population will be adults living in Pakistan with first episode psychosis (FEP) and a carer. In particular, the economic evaluations (i.e., the cost-effectiveness and cost-utility analyses) of the CaCBT and CulFI interventions will be compared to TAU alone. The economic evaluations will be undertaken from the health care sector (i.e., provider and/or third-party payer) and societal perspectives, which is commonly done for economic evaluations undertaken in low- and middle-income countries [37]. The time horizon will be the duration of the trial and the 12-month period after intervention is delivered and, as a result, a discount rate of 5% will be applied, where necessary, in line with the literature [38].

We will quantify the incremental health gains and costs between the three treatment groups. Changes in psychosis symptom severity will be measured using the Positive and Negative Syndrome Scale (PANSS) [32] for the cost-effectiveness analysis, while quality adjusted life years (QALYs) will be assessed using the EQ-5D [39] and the WHO Disability Assessment Schedule (WHODAS) [40] for the cost-utility analysis. Costs will be obtained through a combination of top-down and bottom-up micro-costing approaches. The costs of the intervention will be collected by the team and will include costs associated with staff time, including that of therapists and their training related to intervention delivery, resources and equipment used to deliver the intervention. A bespoke questionnaire will be used to collect data on health care utilization arising due to psychosis and the treatment of patients, other costs to patients (i.e., travel costs) as well as measures of loss of productivity (i.e., absenteeism defined as number of days-off from work due to acute deterioration) over the 12-month period. We will also include the cost of both formal and informal care provided during the trial. We will use standard published sources to obtain unit costs, where available, and supplement these with data from local sources to convert resource use into monetary values. All costs will be adjusted to 2025 Pakistani rupees using appropriate inflators.

For the cost-effectiveness analysis, we will present the results as the cost per psychosis symptom improvement, while for the cost-utility analysis, we will show the results as the cost per quality-adjusted life year gained 12 months after the intervention. Incremental cost-effectiveness ratios will be calculated as the difference in costs between each intervention and the comparator (i.e., treatment as usual alone) groups divided by the difference in benefits/outcomes for economic evaluation. We will also calculate total cost-effectiveness ratios as this has been recommended for LMICs [41]. Standard procedures will be followed for imputation of missing values as well as for the analysis of uncertainty and non-normal distributions. Further statistical analysis of costs will be performed to test for statistical significance of results, while bootstrapping will be performed to estimate variability in key parameters. Relevant deterministic and probabilistic sensitivity analyses will be conducted to understand the robustness of the results and the impact of each parameter on the model’s results. The robustness of each treatment will be shown through 95% confidence intervals around the cost-effectiveness ratio, as well as with for the sensitivity analyses (i.e., discounting of 3%). We will generate a cost effectiveness acceptability curve to summarize the uncertainty in the estimates of the cost-effectiveness analyses [42].

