#### Culturally adapted Family Intervention (CulFI) for psychosis

Participants in the CulFI group will include adults with FEP and their carers, who will receive 10 sessions of 40–60 min, delivered weekly for the first 8 weeks and fortnightly for the remaining 4 weeks. Sessions are delivered to both patients and their carers, though patient participation in sessions is not necessary. CulFI consists of two integrated manuals, *“Schizophrenia: The Indian scene*” [28] and *“Families of schizophrenic patients: Cognitive behavioural intervention”* [29]. CulFI comprises: family psychoeducation; cognitive-behavioural skills training for stress-management, coping and problem solving; crisis intervention and suicide risk management; relapse prevention; and education and support regarding the family environment, including communication training. The components are designed to facilitate an understanding about psychosis, the emotional impact of the illness on family relationships, to promote more adaptive coping strategies and minimize relapse risk. In our pilot study [25] we demonstrated strong recruitment, retention, and large effect sizes on carer well-being and support. Adaptations to the intervention, akin to those outlined above for CaCBT, followed a rigorous cultural adaptation framework based on our prior work in Pakistan [24, 26, 30].

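### The societal cost items name patients' travel only, so carers' travel and time for CulFI sessions risk being left out and CulFI's cost understated against TAU

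*Protocol article*

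**What the plan says.** All cost statements below are in the protocol article, section Cost-effectiveness analysis.

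- **Perspective:** "The economic evaluations will be undertaken from the health care sector (i.e., provider and/or third-party payer) and societal perspectives".
- **Population:** "the target population will be adults living in Pakistan with first episode psychosis (FEP) and a carer".
- **Questionnaire, care use and out-of-pocket costs:** "health care utilization arising due to psychosis and the treatment of patients, other costs to patients (i.e., travel costs").
- **Questionnaire, productivity:** "measures of loss of productivity (i.e., absenteeism defined as number of days-off from work due to acute deterioration"). The text does not say whose absence is meant.
- **Care:** "We will also include the cost of both formal and informal care provided during the trial". Informal care is not defined further.
- **Delivery:** "The costs of the intervention will be collected by the team and will include costs associated with staff time", together with training, resources and equipment. These are the provider's costs.

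On who attends, the section on CulFI states: "Sessions are delivered to both patients and their carers, though patient participation in sessions is not necessary". It schedules 10 sessions of 40 to 60 minutes. The section on CaCBT describes 12 individual patient sessions. The section on treatment as usual says that carers receive no usual care of their own but normally come along to the patient's follow-up visits.

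**The concern.** A societal perspective counts a cost whoever bears it. Here the perspective includes the carer, and one of the two interventions is built around the carer's attendance, yet the out-of-pocket item is worded for patients. The productivity item is triggered by acute deterioration, and a carer who misses work to attend a planned session does not meet that trigger.

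The gap does not fall evenly. CaCBT's session travel is the patient's and is counted. CulFI's session travel is partly the carer's, or wholly so when the patient stays away, and is not clearly counted. At stake is the incremental cost of CulFI over TAU from the societal perspective. That is the numerator of the planned cost-effectiveness and cost-utility ratios and bears directly on the study objective on cost-effectiveness. The health care sector results and the clinical PANSS analysis are not affected.

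**Working it through.** The plan states no cost figure to reproduce, so the check sets each cost item against the carer costs that CulFI sessions create.

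**Step 1: does any listed item capture the carer's cost of attending?**

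| Listed item | Carer's travel to CulFI | Carer's time or lost work for CulFI |
|---|---|---|
| Health care use due to psychosis and patients' treatment | No | No |
| Other costs, with travel named | No: worded for patients | No |
| Absence from work | No | No: tied to acute deterioration |
| Formal and informal care | Not stated | Not stated |
| Delivery costs collected by the team | No: provider side | No: staff time only |

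Only the informal care item could reach these costs, and the text does not say that it does.

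**Step 2: direction of the error.** Let A be the carer's mean cost of attending CulFI sessions per family (travel plus time or lost work), B the carer's mean cost of accompanying a patient to CaCBT sessions, and F the carer's cost of attending routine follow-up visits.

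- CulFI minus TAU: the omitted cost is (A + F) − F = A, if F is the same in both arms. TAU schedules no therapy sessions. CulFI's incremental cost is understated by A, which cannot be negative.
- CulFI minus CaCBT: the omitted cost is (A + F) − (B + F) = A − B. CulFI is understated if A exceeds B. The gap narrows, or could reverse, if carers often accompany patients to the 12 CaCBT sessions. The article does not say how often they do.

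**Step 3: the quantity not named.** Inputs: 10 sessions (8 weekly, then 2 fortnightly, 8 + 2 = 10) of 40 to 60 minutes, and 130 patients per arm. Assumptions: one carer per patient and full attendance.

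- Session time per carer: 10 × 40 / 60 = 6.7 hours to 10 × 60 / 60 = 10 hours.
- CulFI arm: 130 × 10 × 40 / 60 = 867 carer-hours to 130 × 10 × 60 / 60 = 1,300 carer-hours.
- Carer journeys: at most 130 × 10 = 1,300 if every session is held at a site, and none if sessions are held at home.

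These are volumes, not money. Without unit costs, session locations or attendance, A cannot be valued.

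**The case against.** **The questionnaire is not shown.** An article summarises such an instrument in a sentence, and item-level content may properly sit in a fuller document. This limits the point to a risk. It does not remove it, because the article is not silent: it names who bears the out-of-pocket costs and which cost is meant, in a form narrower than the perspective it has just adopted. If the instrument is wider, the sentence needs correcting.

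**Informal care is costed.** This stands in part. Carers' caregiving time is in scope. Whether time spent as a recipient of a family intervention, or travel to it, counts as informal care is left open.

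**Session attendance will be documented.** The section Adherence says so, and those counts would help a later reconstruction. They do not supply fares, travel time or work missed, or show whether a carer came to a CaCBT session.

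A reader might also infer four stronger things that the documents do not support:

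- *That only patients' care and travel are costed.* Productivity loss and formal and informal care are listed as well.
- *That CulFI is understated by a fixed 10 fares per family.* This needs site-based sessions, full attendance and a separate fare for the carer. The Background says illness onset typically occurs while patients live with caregivers, so a shared journey may add little.
- *That unmeasured savings in carers' own health care offset the omission, so that the direction is unknown.* The pilot result cited is "large effect sizes on carer well-being and support", not service use, and the article describes scarce services and no usual care for carers. A saving is conjecture.
- *That counting only psychosis-related contacts is an error.* Disease-related and all-cause costing are a recognised trade-off, and the article does not say that respondents decide the attribution.

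**Conclusion.** The point holds as a mismatch between the stated perspective and the stated cost items. By the wording given, carers' travel and their time or work lost for up to 10 CulFI sessions are not clearly included. The likely effect is to understate CulFI's societal cost against TAU. The same holds against CaCBT unless carers also accompany patients to those sessions.

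The direction against TAU assumes that the informal care item does not cover attendance, that carers come to routine follow-up equally often in both arms, and that attendance costs the carer something. The size in rupees cannot be derived from the document. It could be small if sessions are held at home or journeys are shared. It deserves correction because unrecorded fares and lost work cannot be reliably recovered afterwards, and the planned sensitivity analyses cannot restore a cost that was never collected.

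**What to change.** In the section Cost-effectiveness analysis:

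1. State that travel, other out-of-pocket, and time or productivity costs are collected for the participating carer as well as the patient, and that time or work lost to attend sessions counts whether or not the patient has deteriorated.
2. Ask the same items in all three arms at the existing assessment visits, including carers' attendance at CaCBT sessions and at follow-up visits.
3. Say whether informal care includes attendance at therapy, so that the carer's time is counted once and not twice.
4. Keep the patient-only costing as a sensitivity analysis.

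The carer's own health care contacts could be added at little cost, with no saving presumed. If the questionnaire already covers these items, correcting the text is enough.

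The cost is a few more items in a questionnaire that is being purpose-built anyway, put to carers whose outcomes are already assessed, and slightly longer visits. The sample size and the clinical analyses do not change.

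### The stated cost-effectiveness ratios compare each active arm only with TAU and carry a confidence interval on the ratio; no stated measure uses the CaCBT versus CulFI step

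*Protocol article*

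**What the plan says.** All of this is in the Cost-effectiveness analysis section of the protocol article.

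- **Comparator.** The economic evaluations "of the CaCBT and CulFI interventions will be compared to TAU alone". The ratio is then defined: "Incremental cost-effectiveness ratios will be calculated as the difference in costs between each intervention and the comparator (i.e., treatment as usual alone) groups", over the corresponding difference in outcome.
- **Three-group increments.** "We will quantify the incremental health gains and costs between the three treatment groups". No ratio or decision rule is attached to this sentence.
- **Uncertainty.** "The robustness of each treatment will be shown through 95% confidence intervals around the cost-effectiveness ratio". The section also says that "bootstrapping will be performed to estimate variability in key parameters", plans deterministic and probabilistic sensitivity analyses, and adds: "We will generate a cost effectiveness acceptability curve to summarize the uncertainty in the estimates of the cost-effectiveness analyses".
- **Outcomes.** PANSS change is used for cost-effectiveness. QALYs, from the EQ-5D and WHODAS, are used for cost-utility, with the result 12 months after the intervention.

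**The concern.** Each participant is randomised to exactly one of CaCBT, CulFI or TAU. With three options, the question for a payer is what each further step in cost buys over the next cheaper option still worth considering. Two ratios that share the TAU baseline do not answer it. Both active arms can fall under the threshold while the step from one to the other is poor value, and the arm with the lower ratio against TAU need not have the higher net benefit.

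A confidence interval on a ratio has a separate weakness. When the effect difference may be zero, a Fieller interval is not bounded. A bootstrap percentile interval still returns two numbers, but they order draws that cannot be ordered: a negative ratio may mean cheaper and better, or dearer and worse.

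The article's stated use of the results is scale-up, its objectives include the comparative effect of the two interventions, and its Discussion stresses how little research compares them directly. A reader choosing a programme would need the missing step.

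**Working it through.** **Inputs from the Sample size section.** 390 participants, 130 per arm; 80% power; d = 0.39, equal to 6.70 PANSS points; SD 17.18; 20% attrition. Alpha is not stated there; two-sided 5% is assumed.

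**1. Reproduce the plan's own figure.**
- n per arm = 2 × (1.96 + 0.842)² / 0.39² = 103.2, rounded up to 104.
- 104 / 0.80 = 130 per arm, × 3 = 390. This matches.
- 0.39 × 17.18 = 6.70, and power with 104 per arm is 0.803. Both match.

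**2. How often the ratio interval is not bounded (cost per PANSS point).** A 95% Fieller interval is bounded only if the effect difference is significant at two-sided 5%. In SD units, se = √(2/n), and

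P(not bounded) = 1 − [Φ(d/se − 1.96) + Φ(−d/se − 1.96)].

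For n = 104, se = 0.1387. At d = 0.39, d/se = 2.81 and power is 0.803, which gives 0.197.

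| True d | 104 per arm | 130 per arm |
|---|---|---|
| 0.39 | 20% | 12% |
| 0.30 | 42% | 32% |
| 0.20 | 70% | 64% |
| 0.10 | 89% | 87% |
| 0 | 95% | 95% |

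These are probabilities for each comparison with TAU.

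**3. What a percentile interval would show.** The incremental cost is assumed to be 30,000 with SE 5,000, drawn independently of effect; the documents give no costs. The SE of the PANSS difference is 17.18 × 0.1387 = 2.38. Draws are centred on d × 17.18.
- At d = 0.39 the interval is about 2,270 to 14,400 per point, which is usable.
- At d = 0.20 it is about −59,000 to +80,000, with 7% of draws having a negative effect. The limits exist but have no meaning as an ordered range.

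**4. Ratios against TAU and the choice among three.** All costs, effects and thresholds here are assumed.
- Option A versus TAU: +20,000 cost, 4.0 points gained. Ratio 20,000 / 4.0 = 5,000.
- Option B versus TAU: +40,000 cost, 6.7 points gained. Ratio 40,000 / 6.7 = 5,970.
- B versus A: (40,000 − 20,000) / (6.7 − 4.0) = 7,407.

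Net benefit = threshold × effect − cost:

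| Threshold per point | A | B | Better value |
|---|---|---|---|
| 6,500 | 26,000 − 20,000 = 6,000 | 43,550 − 40,000 = 3,550 | A |
| 8,000 | 32,000 − 20,000 = 12,000 | 53,600 − 40,000 = 13,600 | B |

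At 6,500 both options pass against TAU, and taking the more effective one picks B, which is wrong. At 8,000 taking the lower ratio against TAU picks A, which is wrong. The B versus A ratio of 7,407 settles both cases. The two ratios that the plan defines are the same in both rows, so neither simple rule applied to them is reliable.

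**The case against.** The best defence is that much of what is needed is already planned. Increments among all three groups are promised, and the CaCBT versus CulFI ratio follows from them by one division. Bootstrapping, probabilistic sensitivity analysis and an acceptability curve are named, and such a curve does not depend on ordering ratios across quadrants. The section also plans total cost-effectiveness ratios. TAU is the reference for the primary contrast, and CaCBT versus CulFI is exploratory. Guidelines are said to endorse both therapies for all patients, and the Discussion notes that FI can help where the patient does not engage, so the two need not be rivals in practice. The finer steps of a health-economics analysis are often left to a fuller plan.

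Much of this stands and limits the point. A reader might infer that the plan ignores the active-arm comparison, or that the ratio interval is its only view of uncertainty. The text supports neither. A reader might also call the intervals undefined. The interval method is not named, and a bootstrap always returns numbers; unbounded (Fieller) or uninterpretable (percentile) is the accurate description.

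What does not stand is the appeal to omitted detail. The comparator of the ratio and the interval on the ratio are stated rules. The three-group sentence leads to no ratio or dominance step. The curve answers the choice among options only if it is built jointly, which is not said. No arm combines the two therapies, so this trial can inform only a choice among its three options.

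**Conclusion.** The point holds in a limited form. As stated, the ratios and their intervals can leave the best-value option unidentified, and the interval will often be unusable if the true effect is below the design value. For cost per PANSS point the chance is about 20% at d = 0.39 with 104 analysed per arm, 12% if all 130 contribute fully, and 70% at d = 0.20 with 104. This rests on two-sided 5%, the 3-month SD and attrition carried to the time of the economic analysis, the effect expressed per PANSS point, and no gain in precision from baseline adjustment or repeated measures, which would lower the figures.

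It would be tempting to apply the 20% to the cost-utility result. The documents do not allow that: they give no QALY variability and no power at 12 months after the intervention. Nor do they show that the wrong programme would be scaled up, since they contain no costs or threshold; the cost examples show only that the error is possible. The point affects a secondary, economic objective and leaves the primary analysis untouched.

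**What to change.** In the health-economics plan:

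1. Keep the two ratios against TAU, and add a fully incremental analysis of the three options: order by cost, remove dominated and extendedly dominated options, and report sequential ratios.
2. Replace the confidence interval on the ratio with incremental net benefit and its bootstrap 95% interval over a stated range of thresholds, for PANSS points and for QALYs.
3. State that the planned acceptability curve is built jointly from the same bootstrap draws for all three options, so that the three probabilities sum to 1 at each threshold.
4. Label the CaCBT versus CulFI step as exploratory and imprecise.

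The cost is a few lines of text and a little more analysis on the same data and bootstrap. Data collection and sample size do not change. The drawback is that the step between the active arms will carry wide uncertainty, which the report should say plainly.

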#### Process evaluation

Process evaluation will be guided by the Consolidated Framework for Implementation Research (CFIR) that will inform formative evaluation and help to build the implementation knowledge base for proposed interventions across study settings [43]. We will purposively sample up-to 15 patient-carer dyads from each treatment arm (total 30 patient-carer dyads) ensuring maximum variation and diversity (age, gender, socioeconomic status, and geographical location) and up to 15 patient-carer dyads who ‘drop out’ before completion (total 30 patient-carer dyads). Based on our previous experience [44] and published evidence [45], we are confident that we will achieve data saturation [46] with these numbers of interviews. We will interview all trial therapists for both interventions to explore experiences of delivering interventions, barriers and facilitators, the content and phrasing of discussions with patients and carers, and their views about approaches that work best and least. Transcripts will be analyzed using the Framework analysis [47] incorporating both inductive and deductive coding. The deductive coding will be informed by the CFIR with inductive coding ensuring no relevant data is lost.

### Ethical considerations

The authors assert that all procedures contributing to this work comply with the ethical standards of the relevant national and institutional committees on human experimentation and with the Helsinki Declaration of 1975, as revised in 2008. All procedures involving human subjects/patients were approved by the National Bioethics Committee of Pakistan (Ref: No.4-87/NBC-905/23/1199) and the Centre for Addiction and Mental Health (CAMH) Research Ethics Board, Toronto, Canada (REB # 2023/017). All members of the research team will comply with the International Conference on Harmonization Good Clinical Practice (ICH-GCP) Guideline. Research staff will be trained in good clinical practice (GCP) and will not begin data collection until the GCP certification is successfully completed. All information provided by the participants will be kept confidential and authorization will be required prior to accessing data. Patient-identifying information will not be published. Privacy and confidentiality of participants will be maintained. Participation in the trial will be voluntary and participants will have the right to withdraw from the study at any time, for any reason. Withdrawal from the trial will have no effect on routine care.

